## Abstract

**Rationale/aim:**

Despite the increasing efficacy of recanalization therapies for acute ischemic stroke, a large number of patients are left with long-term functional impairment, devoid of efficacious treatments. CD34+ cells comprise a subset of bone marrow-derived mononuclear cells with the capacity to promote angiogenesis in ischemic lesions and have shown promising results in observational and *in vitro* studies. In this study, we aim to assess the efficacy of an autotransplant of CD34+ cells in acute ischemic stroke.

**Sample size estimates:**

30 patients will be randomized for a power of 90% and alpha of 0.05 to detect a difference in 3 months infarct volume.

**Methods and design:**

We will screen 18–80 years old patients with acute ischemic stroke due to occlusion of a middle cerebral artery (MCA) for randomization. Persistent arterial occlusions, contra-indications to magnetic resonance imaging (MRI), premorbid dependency, or other severe diseases will be excluded. Treatment will involve bone marrow aspiration, selection of CD34+ cells, and their administration intra-arterially in the symptomatic MCA by angiography. Patients will be randomized for treatment at 7 (±2) days, 20 (±5 days) or sham procedure, 10 in each group.

**Study outcomes:**

The primary outcome will be infarct volume in MRI performed at 3 months. Secondary outcomes will include adverse events and multidimensional functional and neurological measures.

**Discussion/conclusion:**

STROKE34 is a PROBE design phase IIa clinical trial to assess the efficacy of intra-arterial administration of CD34+ cells 7 and 20 days after acute ischemic stroke.

**Trial registration (EU Clinical Trials Register):**

2017-002456-88.

## Introduction and Rationale

Current treatment algorithms for ischemic stroke have their primary focus on promoting vascular reperfusion, leaving tissue recovery devoid of directed and efficient therapies. In fact, despite the increasing efficacy of recanalization methods, up to half of patients who survive ischemic stroke develop long-term functional impairment. To overcome this therapeutic need, cell therapies have emerged as a potential method of promoting neurological recovery (1–5). However, many quandaries still limit their translation into clinical practice, especially in therapies aiming at neuro and synaptogenesis (6). Recently, CD34+ cells have shown promising results in observational and *in vitro* studies, urging research translation into randomized trials (7–9). They comprise a subset of bone marrow-derived mononuclear cells representing the main source of endogenous endothelial progenitor cells (EPC), with the capacity to promote angiogenesis in ischemic injuries. A phase I clinical trial demonstrated the safety and feasibility of administering intra-arterially autologous, bone marrow-derived CD34+ cells (10). We aim to design a phase IIa clinical trial to evaluate the efficacy of the intra-arterial administration of CD34+ at two timepoints: 7 ± 2 and 20 ± 5 days.

## Methods and Analysis

### Design

STROKE34 is a phase IIa superiority, unicenter, randomized, blinded outcome assessment, sham-controlled clinical trial evaluating the efficacy of intra-arterially administered CD34+ cells 7 ± 2 and 20 ± 5 days after ischemic stroke (PROBE design).

### Patient Population

We will screen for inclusion consecutive patients with non-lacunar acute ischemic stroke infarctions within the territory supplied by a middle cerebral artery (MCA). In Table 1, we present the study’s inclusion and exclusion criteria. Demonstration of arterial recanalization at the time of inclusion will be determined by angiography (modified TICI grades 2b or 3) or transcranial color coded Doppler (TIBI grades 4 or 5) (11, 12).

**Table 1 T1:** Inclusion and exclusion criteria for the study.

Inclusion criteria	Exclusion criteria
Age 18–80 years; Acute hemispheric ischemic stroke attributable to injury within the territory supplied by the middle cerebral artery; Symptomatic arterial territory is recanalyzed; Onset of an acute ischemic stroke that can have full clinical, imagiological, and bone marrow collection within 7 days after onset. Onset is defined as the time that the subject was last seen in a normal state, or bedtime for unwitnessed strokes occurring during sleep; Readily accessible peripheral venous access blood sampling; Ability to understand the requirements of the study and be willing to provide written informed consent, as evidenced by signature on an informed consent document, agreeing to perform the required assessments. In the event of incapacitated subjects, informed consent will be sought from a legally acceptable representative.	Patients found delirious, comatose, demented or having any mental impairment other than the neurological deficits related to the index stroke that in the investigator’s opinion renders the subject incapable to participate in the study; Presence of high-grade (>70%) internal carotid artery stenosis or occlusion ipsilateral to the current stroke. Inflammatory disease present at baseline (chronic systemic inflammatory disease active at the time of inclusion or acute inflammatory disease such as an infection); Active malignancy, or recent surgery (within the previous 3 months); Premorbid neurological deficits and functional limitations assessed by a premorbid Modified Rankin Scale (mRS) score >2; Presence of a severe co-existing disease that may interfere with the conduct of the study, irrespective of stroke outcome; Known pregnancy. Females of childbearing potential will be screened at baseline with urine pregnancy test and positive results will be excluded [the choice of excluding pregnancies is due to the relative contra-indication to magnetic resonance imaging (MRI) in these patients]; Contra-indication to MRI. Allergy to contrast agents.

### Randomization

Subjects will be randomized, stratified for age, gender, baseline NIHSS (at randomization), laterality and performance of recanalization therapies (intravenous or intra-arterial) into intervention at day 7 ± 2; intervention at day 20 ± 5; sham procedure at day 7 ± 2; sham at day 20 ± 5, in a 2:2:1:1 ratio, using a computerized stratified randomization program (Figure 1).

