### Sample Size Estimates

No human randomized trials are available for effect estimate on intra-arterial administration of CD34+ for acute ischemic stroke. Moreover, animal studies are not ideal considering the specificity and inherent heterogeneity of human subjects. As such, for sample size calculation, we have used data from human observational studies on EPCs (7, 13). These studies indicated a large effect of EPCs in final ischemic lesion volume, with reported treatment effect sizes ranging from 1.2 to 2.0 (7, 13). For our sample size calculation of a unicenter pivotal phase IIa trial, we used an effect size of 1.2 for 90% power and a significance level of 5% to identify a difference between independent means of final infarct volume. A total of 30 patients was estimated for the trial: 10 patients treated at day 7 ± 2, 10 at day 20 ± 5, and 10 in the control group (5 sham procedures at each timepoint to ensure blinding).

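### Stratifying 30 patients on five factors gives at least 32 strata, so ordinary blocks within strata would balance the factors little and would not secure the 10/10/10 (5+5 sham) group sizes

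*Protocol article*

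**What the plan says.** All of this is in the protocol article under Methods and Analysis.

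- **Randomization**, factors: "stratified for age, gender, baseline NIHSS (at randomization), laterality and performance of recanalization therapies (intravenous or intra-arterial").
- **Randomization**, groups: "intervention at day 7 ± 2; intervention at day 20 ± 5; sham procedure at day 7 ± 2; sham at day 20 ± 5".
- **Randomization**, method: "in a 2:2:1:1 ratio, using a computerized stratified randomization program". No algorithm, block size, cut-points for age or NIHSS, or cap per group is given.
- **Sample Size Estimates**: "A total of 30 patients was estimated for the trial". Each of the two active groups is to have ten patients; the remainder are "10 in the control group (5 sham procedures at each timepoint to ensure blinding").
- **Design**: the trial is single-centre, so centre adds no strata.

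**The concern.** Stratified randomization works by filling blocks within each stratum. When there are more strata than patients, few blocks fill. The imbalances left in the unfinished blocks then add up across strata, and neither the factor balance nor the overall group sizes are controlled.

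Two things are at stake. First, the five factors were chosen so that small groups would be comparable, and with about 10 patients per group chance imbalance matters. Second, the plan counts on specific sizes: about 10 in each active group, since the Discussion hopes to say which time window is preferable, and 5 sham procedures in each window, which the Sample Size Estimates section gives as a means of protecting the blinding. The randomization rule as stated would not deliver either.

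Cut-points and block size may well be in the full protocol, and their absence from an article is not the fault. The fault is the stated combination of five factors and 30 patients, which no choice of cut-points can bring below 32 strata.

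**Working it through.** **1. The plan's own figures.** With effect size 1.2, 90% power and 5% significance (two-sided assumed; sidedness is not stated), the normal approximation gives n per arm = 2 × (1.960 + 1.282)² / 1.2² = 14.6, so 15, and 2 × 15 = 30. This reproduces the total as a two-group 1:1 comparison. Applying 2:2:1:1 to 30 gives 30/6 = 5 per unit, so 10:10:5:5, which matches the stated sizes.

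**2. Strata.** A stratification factor has at least two levels.

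- Minimum: 2^5 = 32 strata, or 30/32 = 0.94 patients per stratum.
- Recanalization therapy with three levels: 2^4 × 3 = 48.
- Age, NIHSS and recanalization with three levels each: 2² × 3³ = 108.

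The four allocation groups do not add strata. They set the smallest complete block, 2 + 2 + 1 + 1 = 6.

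**3. How thin the strata are** (32 equally likely strata). Expected occupied strata: 32 × [1 − (31/32)^30] = 19.7. Chance that a patient is alone in a stratum: (31/32)^29 = 0.40. The chance that any stratum reaches six patients is 0.9% by simulation. It rises to about 6% with moderately uneven factor splits and to about 80% with 75/25 splits on all five factors.

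**4. Group sizes.** Simulation of 30 patients with permuted blocks of 6 (2:2:1:1) in each stratum. The documents give no prevalences, so two cases are shown for the range. Sham total means both sham windows together.

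| | Five factors, 50/50 | Five factors, 75/25 | Simple randomization |
|---|---|---|---|
| Exactly 10/10/10 | 3.3% | 4.7% | 2.6% |
| Exactly 10/10/5/5 | 0.9% | 1.4% | 0.6% |
| All three groups within 1 of 10 | 21% | 29% | 17% |
| Some group of 7 or fewer | 41% | 29% | – |
| A sham window of 3 or fewer | 39% | 32% | – |
| Sham total, 95% range | 5–15 | 6–14 | 5–15 |

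Repeat runs differ by about a point. Exact check on the last column: 30!/(10!)³ / 3^30 = 2.7%.

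**5. Balance.** Mean absolute difference between the day-7 and sham groups in the proportion at one level of a factor:

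- 50/50 splits: 0.169 stratified, 0.186 simple; 1 − 0.169/0.186 = 9% lower.
- 75/25 splits: 0.134 stratified, 0.161 simple; 1 − 0.134/0.161 = 17% lower.
- For reference, 50/50 splits: one unstratified list of blocks of 6 gives 0.176; minimization on the five factors gives 0.101.

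**6. Power.** Two-sided t-test, effect size 1.2, averaged over the group sizes that the five-factor scheme produces with equal strata:

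- Pooled active against sham: 83.3%, against 84.9% at fixed 20 and 10.
- Day 7 against sham: 69.4%, against 71.8% at fixed 10 and 10.

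The losses are about 1.5 and 2.4 points; with 75/25 splits they are about 1.1 and 1.6 points.

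**7. Alternatives.**

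- Minimization on the same five factors (best group chosen with probability 0.8, otherwise a random draw at 2:2:1:1): all three groups within 1 of target in about 93 to 94% of trials.
- One two-level factor with blocks of 6: no group of 7 or fewer, and exact 10/10/10 in 39%.

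**The case against.** **The mechanism is assumed.** The article says only that a computerized stratified program is used, and a condensed article need not describe the algorithm. With minimization or a cap per group, the size problem would largely go away. This stands as a condition on the size figures. It does not remove the point, because the literal wording is stratified and the strata count cannot fall below 32.

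**Equal strata are an extreme case.** This stands, which is why a range is shown. Even with 75/25 splits on every factor, where a block often fills somewhere, exact 10/10/10 is below 5% and all three groups are within 1 of target in fewer than 30% of trials.

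**Stronger readings that the documents do not support:**

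- A reader might infer that the stratification balances nothing. It does reduce imbalance, by about 9 to 17%.
- A reader might infer that the trial loses substantial power, or is biased, because of this. The average loss is about 1 to 2.5 points, and chance differences in size or covariates do not bias a randomized comparison. The 30 patients give about 90% power only as 15 against 15; that is a separate matter and lends this point no weight.
- A reader might infer that leaving out baseline infarct volume is an error. A pre-treatment MRI is planned, but the article neither calls volume the strongest predictor nor says that a measured volume exists at randomization. Baseline NIHSS, a severity measure, is already a factor.

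**The trial is exploratory and admits its small sample.** True, and it limits how much weight the point carries. But small groups are where a working balancing method helps most.

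**Conclusion.** The concern holds in this form: a rule stated in the plan works poorly at the planned size. That there are at least 32 strata for 30 patients, against a smallest block of 6, depends on no assumption beyond two levels per factor. The consequences for size and balance depend on ordinary permuted blocks of 6 within strata and on factor splits between 50/50 and 75/25. Under those assumptions the scheme is only slightly better than simple randomization. A group of 7 or fewer would arise in roughly three to four trials in ten, and a sham window of 3 or fewer in about a third or more.

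The harm is mainly prognostic balance that is not delivered and a 5 + 5 sham split that is not protected, with a minor effect on average power. It should be corrected because the remedy is cheap, not because the trial's validity turns on it.

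**What to change.** Choose one of the following before the first patient is randomized:

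1. **Minimization with a random element** over the same five factors, at 2:2:1:1, with the factor levels and the probability of the preferred group fixed in advance. This keeps every factor the sponsor wanted.
2. **Stratification on one factor**, for example baseline NIHSS at a fixed cut, with permuted blocks of 6. The other factors are then used as covariates in the analysis, as far as 30 patients allow.

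If the program already uses minimization or limits the size of each group, no change of method is needed for the sizes. The Randomization section should then name that method in place of the present description.

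The cost is reprogramming the randomization system and rewriting one paragraph. The downside is some predictability of the next allocation at a single centre; with minimization, the random element limits it.

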**Figure 1 F1:**
[figure not shown]
Trial design flow chart. Abbreviations: MRI, magnetic resonance imaging; d, days.

### Intervention

First, a single-pull 10-mL aspirate of bone marrow from the iliac crest will be collected by experienced Hematologist under aseptic conditions, using only local anesthesia at puncture site. CD34+ cells will then be isolated by magnetic cell sorting using CliniMACS Plus^®^ (Miltenyi Biotec) without cellular manipulation and suspended in 10–100 mL of saline solution. 24–48 h after collection, 1 × 10^6^ up to 1 × 10^8^ cells suspended in human albumin solution will be administered intra-arterially in the symptomatic MCA (Figure 2). Before infusion, all solutions will be screened for infections according to national human tissue transplantation requirements (national legislation 12/2009): Syphilis, HIV 1 and 2, Hepatitis B and C in all patients, as well as human T lymphotropic virus 1 and 2 whenever indicated.

**Figure 2 F2:**
[figure not shown]
Illustrative representation of autotransplant of CD34+ cells. In the top of the image, bone marrow aspiration by hematologist is represented. The second step (bottom right) is the isolation of CD34+ cells, followed by the intra-arterial administration of the CD34+ in the symptomatic MCA (bottom left). Abbreviation: MCA, middle cerebral artery.

In the angio-suite, catheterization of the symptomatic MCA by neuroradiologist will follow routine practice. In short, all patients will initially be submitted to local anesthesia of the groin for femoral artery puncture and intravenous administration of 5,000 units of unfractionated heparin. Then, a guide catheter selected according anatomical features of the patient will be navigated up to the initial segment of the symptomatic internal carotid artery. At that point, a microcatheter will navigate up to the beginning of the M1-MCA, where the solution containing the CD34+ cells will be slowly infused during approximately 10 min. The expected total duration of the procedure will be 30 min. All procedures will be accompanied by anesthesiologist. Sedation will not be used routinely, but will be possible according to the anesthesiologist’s choice. No other drug will be used routinely during the procedure, but the treating physicians will be free to use any other treatment considered necessary according to clinical condition. In case the interventionalist encounters a previously undiagnosed high-grade stenosis (>70%), vascular occlusion or any vascular malformation in the symptomatic arteries considered to be potentially hazardous in case of catheterization the treatment will be aborted.

Patients in the sham group will initially be subject to local anesthesia of the iliac crest by Hematologist (without bone marrow aspiration) and brought to the angio-suite 24–48 h later. All study participants will be blindfolded during the angiographic procedure and submitted to local anesthesia of the groin. Patients in the sham group will not be subject to arterial puncture and will remain in the angio-suite for approximately 30 min simulating cellular infusion. No information about treatment allocation will be transferred to the recovery staff at stroke unit. Subsequent medical caregivers will also be blinded to treatment allocation. The study physicians present during the angiographic procedure will have no further contact with the patient during the study.

Until clinical stabilization, the patients will remain in the hospital and perform a control magnetic resonance imaging (MRI) 48 h after treatment, followed by orientation by a dedicated rehabilitation center.

### Allocation Concealment

Stroke unit staff, patients, and outcome assessors are blinded to treatment allocation for the duration of the study. Unblinding will only take place whenever the treating physician decides that clinical management will critically depend on knowledge of treating allocation. Unblinding will be monitored and audited.

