### Outcomes Assessed

The primary outcome will be ischemic stroke volume, measured by automated planimetric method on FLAIR imaging sequences of MRI performed 3 months after index event. The secondary outcomes are presented in Table 2. Neuroimaging assessment will include analysis of the three MRI performed during the study: before treatment, 48 h after treatment, and at 3 months. The neuroradiologist that will evaluate lesion volumes and physicians that will evaluate the secondary outcomes will not be involved in the initial management of the patient nor intervention and will be blinded for treatment allocation.

**Table 2 T2:** Study outcomes assessed.

Primary outcome
Ischemic stroke volume on magnetic resonance imaging (MRI) performed at 3 months

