Another critical point in the design of this trial is the choice of therapeutic time window. Angiogenesis after stroke has been demonstrated from 3 to 4 days up to 5 weeks after injury (16–18). However, it is still unknown when CD34+ transplantation would be clinically effective. Early administration would imply exposing the highly active and metabolically demanding CD34+ cells to an inhospitable ischemic environment and would potentially promote ineffective angiogenesis and hemorrhagic transformation. Moreover, within the first 24 h, bone marrow aspiration would be contra-indicated in patients submitted to intravenous thrombolysis. Nonetheless, it is uncertain if later time windows would still have any clinical meaning, and the need for a permeable blood–brain barrier will ultimately limit cell delivery beyond the first 5 weeks (19). Altogether, a wide time frame is still potentially usable (from the first days up to 5 weeks) with presumably different biological effects and clinical implications. In this trial, we hope to answer if an earlier time window (5–9 days) is preferable compared to a later window (15–25 days).

A potential limitation of this study design is the small sample size planned. However, we have defined the primary endpoint as a neuroimaging variable (3 months infarct volume), to allow the inclusion of a smaller number of patients in this exploratory phase IIa trial, and have included comprehensive functional assessments as secondary outcomes.

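### The stated blind cannot cover early v late treatment for patients and stroke unit staff: the procedure date reveals the window, and only active v sham within a window is blinded

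*Protocol article*

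**What the plan says.** The Randomization section makes the treatment window part of what is allocated. Beside the two active groups it lists "sham procedure at day 7 ± 2; sham at day 20 ± 5, in a 2:2:1:1 ratio". Sample Size Estimates gives 10 patients treated in each window and "10 in the control group (5 sham procedures at each timepoint to ensure blinding".

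Allocation Concealment then says, without limiting the statement to active v sham: "Stroke unit staff, patients, and outcome assessors are blinded to treatment allocation for the duration of the study".

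The means of blinding are in the Intervention section. Sham patients receive local anaesthesia at the iliac crest and the groin and spend a comparable time in the angio-suite. "All study participants will be blindfolded during the angiographic procedure and submitted to local anesthesia of the groin". The patient is normally awake: "Sedation will not be used routinely".

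Outcomes Assessed says of imaging: "Neuroimaging assessment will include analysis of the three MRI performed during the study: before treatment, 48 h after treatment, and at 3 months". It adds that the neuroradiologist and the physicians who assess secondary outcomes are blinded and take no part in initial management or the intervention. The primary outcome is the 3-month FLAIR volume, timed from the stroke and measured by an automated method.

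The Discussion makes the comparison of windows a question for the trial: "we hope to answer if an earlier time window (5–9 days) is preferable compared to a later window (15–25 days".

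**The concern.** The trial asks two things: whether the cells work, and whether early or late delivery is preferable. The sham answers the blinding need of the first. Nothing described answers it for the second, because a patient who goes to the angio-suite once knows the day, and so does the unit that receives that patient back. The blinding statement nevertheless covers the whole allocation.

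At stake is how a window difference may be interpreted. Several secondary outcomes rest on the patient's own answers (Stroke Impact Scale, Hospital Anxiety and Depression Scale, EQ-5D) or on effort during testing (gait, MoCA). A reader who takes the statement at face value would treat a window difference on these as a blinded result. It would in fact come from patients, and from care given by staff, who knew the window. The Discussion says the work should help define the window for phase III, so the distinction matters for what follows.

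**Working it through.** **Inputs.** Four groups in ratio 2:2:1:1 (Randomization); 30 patients, split 10, 10 and 10 with 5 shams at each timepoint (Sample Size Estimates); windows 7 ± 2 and 20 ± 5 days, written out as 5–9 and 15–25 (Discussion); control MRI 48 h after treatment (Intervention, Outcomes Assessed); final MRI 3 months after the stroke (Outcomes Assessed).

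**1. The plan's own split.** The ratio parts sum to 2 + 2 + 1 + 1 = 6. Active groups: 30 × 2/6 = 10 each. Sham groups: 30 × 1/6 = 5 each. This agrees with the stated numbers and shows that the window is a randomised factor in every patient, sham patients included. No sample-size figure is in dispute here.

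**2. Do the windows overlap?** Early: 7 − 2 = 5 to 7 + 2 = 9. Late: 20 − 5 = 15 to 20 + 5 = 25. Smallest gap: 15 − 9 = 6 days. For a patient treated as planned:
- P(early | procedure on days 5–9) = 1
- P(late | procedure on days 15–25) = 1

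The date of the procedure fixes the window. A dummy procedure at the other time would break this link, but none is described. The shams are split between the timepoints instead.

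**3. Does the window reveal active v sham?** Within the early window there are 10 active and 5 sham patients, so P(active | early) = 10/15 = 2/3. Within the late window P(active | late) = 10/15 = 2/3. Overall P(active) = 20/30 = 2/3. Knowing the window leaves the chance of active treatment unchanged, so that part of the blind is intact.

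**4. Who necessarily knows the window?** Patients do: the blindfold and groin anaesthesia hide what was done, not the day, and sedation is not routine. Stroke unit staff do: the patient returns to them after the procedure. Withholding information on allocation does not conceal the date of a transfer they took part in.

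**5. What would the scans show, if dated?** The 48-h scan falls 2 days after treatment:
- early: 5 + 2 = 7 to 9 + 2 = 11
- late: 15 + 2 = 17 to 25 + 2 = 27

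These ranges do not overlap. Taking 3 months as day 90 (an assumption), the interval from the 48-h scan to the final scan is:
- early: 90 − 11 = 79 to 90 − 7 = 83 days
- late: 90 − 27 = 63 to 90 − 17 = 73 days

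A reader given the dates of the serial scans could therefore tell the window. The 3-month scan alone could not show it, since it is timed from the stroke in every group. The pre-treatment scan is less clear. It is placed only before treatment, and Table 1 requires imaging within 7 days of onset, so it may be of similar age in all groups.

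**6. Side by side.**

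| Comparison | Patients and stroke unit staff | Reader and assessors |
|---|---|---|
| Active v sham within a window | Blinded by window-matched sham | Stated as blinded; nothing here contradicts it |
| Early v late | Necessarily known | Can be blinded; depends on masking of dates, which is not described |

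**The case against.** **The statement may mean only active v sham.** The shams are placed at each timepoint expressly for blinding. The emergency unblinding rule also makes sense only for active v sham, since the treating team already knows the procedure date. This is probably what was intended. The sentence does not say so, however, and the allocation it refers to includes the window.

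**A reader might infer that the neuroradiologist and the 3-month assessors are also unblinded to the window, so that the primary outcome is compromised.** The article does not support this. It says these people are blinded, and it does not say that they see scan or procedure dates or read the three scans together. Date masking and reading order are details that an article may leave to the full protocol. The pre-treatment scan need not differ in age between groups, and the flow chart is not shown. The primary measure is automated and comes from a scan that does not reveal the window. What stands is a conditional risk, concentrated on the 48-h scan and on the secondary outcome that uses it.

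**A reader might also infer that open timing weakens the active v sham comparison.** It does not: the chance of active treatment is 2/3 in both windows.

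**The route to bias is weak.** Expected Results says that existing data give no rational basis for preferring a window, the Discussion gives drawbacks of both, and patients do not know whether they received cells. This stands as a reason why neither direction nor size can be claimed. It does not make the comparison blinded: patients and staff may still hold expectations, and the outcomes listed can respond to them.

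**Open timing is inherent in comparing two windows with one procedure each.** That is true, and no redesign is called for. It is a reason to state the limit plainly.

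**Conclusion.** The point holds for patients and stroke unit staff. Allocation Concealment claims a property that the design does not have for one of the trial's stated questions. It concerns all 30 patients, because the windows are at least 6 days apart and the procedure date fixes the window each time.

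The consequence is bounded. Early v late is open for patient-reported and effort-dependent secondary outcomes (Stroke Impact Scale, Hospital Anxiety and Depression Scale, EQ-5D, gait, MoCA). Active v sham within a window remains protected by the sham design. The 3-month automated FLAIR volume does not itself reveal the window. Blinding of the reader and assessors to the window is achievable; it would fail only if scan or procedure dates were visible to them, which the article does not say.

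The size and direction of any bias cannot be derived from the article. The conclusion assumes that patients are treated within their windows and that no dummy procedure at the other time exists beyond what is described. No sample-size figure changes.

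**What to change.** 1. Restate Allocation Concealment: patients and stroke unit staff are blinded to active v sham within a window, and are not blinded to the window.
2. So that the assessor blinding stated in Outcomes Assessed also holds for the window, read the 3-month FLAIR with dates removed and separately from the earlier scans. Remove dates from the pre-treatment and 48-h scans as well, and keep the procedure date from the physicians who assess outcomes at 3 months. If the full protocol already provides for this, a sentence saying so is enough.
3. Rest any early v late conclusion on the imaging outcome read in this way, and label window comparisons on patient-reported outcomes as unblinded.

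The cost is wording and routine image de-identification. No additional patients, procedures or scans are needed.
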